### Secondary outcome and other study measures

We will also evaluate several secondary outcomes. These will include an additional measure of receipt of test results based on medical records. Study participants will complete release forms (as applicable) in order to grant permission to study staff to review their medical records, including HIV and HCV testing records. Other secondary outcomes will include self-reported sexual risk behaviors and drug use practices such as (i) counts of unprotected vaginal and anal sex acts in the past 3 months with any sex partner, (ii) use of any drugs in the past 3 months, and (iii) unsafe injection practices. Additional measures will evaluate linkage to care by measuring the proportion of patients who initiated HIV care or HCV care before the 3-month follow-up among those whose test results were positive for HIV and/or HCV. Linkage to care for HIV or HCV will be measured separately, to account for variations in barriers to initiating care, which may be greater for HCV than barriers to initiating HIV medical care [67].

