### Power and sample size

We designed the trial to estimate the effects of on-site bundled rapid HIV/HCV testing on receipt of test results separately in each of the two types of SUD treatment facilities (MTAA and CDOP). Based on preliminary data from the study sites for the standard of care, we assumed that 50 % of control group participants enrolled at the CDOP facility will receive their HIV and HCV results after 1 month. We assumed that 55 % of control group participants receive their HIV and HCV test results after 1 month in the MTAA program, which treats a higher proportion of PWIDs. Based on findings from the evidence-based rapid HIV intervention that informs this study [25], we assumed that 80 % of patients in the intervention group would receive their HIV and HCV test results within 1 month of randomization. To detect such intervention effects on the basis of a two-sample, chi-squared test for independent proportions with 80 % power and α = 0.05, we will require 78 patients in CDOP and 108 patients in MTAA facilities. We assumed an 80 % follow-up rate among participants enrolled at the MTAA program. We assumed a slightly lower follow-up rate among participants enrolled at the CDOP facility (75 %) because adherence to behavioral SUD treatment is lower among CDOP patients at Promesa Inc. These are conservative assumptions. For example, during the trial of the rapid HIV testing EBI, which informs this study, researchers achieved a 98 % 1-month follow-up rate [25]. In total, we obtained a total sample size of 239 participants (104 in CDOP and 135 in MTAA).

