### Empirical analysis

The primary outcome is a categorical variable denoting self-reported receipt of rapid HIV and rapid HCV test results at 1-month post-randomization. We will use a generalized estimating equation model, which includes covariates for type of drug use (injection/non-injection) and location of primary care provider (study site versus elsewhere). The model will also include indicator variables for HIV/HCV testing intervention status and the type of SUD treatment facility (MTAA versus CDOP), where the participants were recruited. The primary test of our study hypothesis will be a two-degree of freedom test of significance of the intervention across the two types of SUD treatment facilities. In post-hoc tests, the efficacy and effect size in each type of SUD treatment facility will be examined. To do so, we will include an interaction between variables identifying study groups (intervention versus control) and type of SUD treatment facility (MTAA versus CDOP). The primary analysis will be intent-to-treat, where everyone is included in the study group to which they were randomized, regardless of receipt of intervention. In sensitivity analyses, participants who have died or who have been lost to follow-up will be counted as not having tested. We will adjust for baseline covariates that may be associated with attrition from the study sample using inverse probability reweighting procedures as recommended for the GEE model [69].

The secondary outcomes related to linkage to HIV and HCV care, as well as to drug use, are categorical variables. They will be analyzed using techniques similar to those used for the primary outcome. This is also the case for indicators related to HIV and HCV prevalence among patients tested by bundled rapid testing versus standard of care. The number of unprotected sex acts over a period of time is a count variable and will be modeled using Poisson or negative binomial regression (if the variable is over-dispersed) or the zero-inflated version of these if necessary. Type of drug use (injection/non-injection) and the recruitment site (MTAA or CDOP) will be included as covariates. If other covariates predict missing data, they will also be included as control variables. All analyses of secondary outcomes will focus on the pooled data, that is, CDOP + MTAA programs. Because of the limited sample size, we will not conduct formal mediation analyses.

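### Secondary count of unprotected sex acts: the optional zero-inflated branch changes the effect measure, and no coefficient is named as the treatment effect

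*Protocol article*

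**What the plan says.** The section on secondary outcomes in the protocol article defines the endpoint as "counts of unprotected vaginal and anal sex acts in the past 3 months with any sex partner". The Empirical analysis section then says this count "will be modeled using Poisson or negative binomial regression (if the variable is over-dispersed) or the zero-inflated version of these if necessary".

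The move to negative binomial has a stated trigger, over-dispersion. The move to a zero-inflated version is left to need. The text does not say which coefficient of a zero-inflated fit would be the treatment effect.

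The covariates listed after this rule are type of drug use and recruitment site. A further clause reads: "If other covariates predict missing data, they will also be included as control variables". The Randomization section stratifies by three factors: recruitment site, type of drug use, and location of the primary care provider. The primary model includes all three; the list given for the secondary models leaves out the last.

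On the data set, the article says "All analyses of secondary outcomes will focus on the pooled data, that is, CDOP + MTAA programs". The stated alpha, power and sample size refer only to receipt of HIV and HCV test results.

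**The concern.** The rule lets the outcome data decide which question is answered. On the Poisson or negative binomial branch, the result is one number: the ratio of mean acts between arms. On the zero-inflated branch there are two numbers, each about a different part of a latent mixture, and neither is the effect on mean acts.

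Two things follow if nothing further is fixed. First, a report that gives only the count part could show no effect when mean acts have fallen because more participants report none. Second, two arm coefficients offer two chances to claim a result.

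The outcome is secondary, but it is not idle: the Discussion names safer sexual practices as one route by which the strategy might reduce transmission.

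**Working it through.** **1. The article's own figures.** It gives no figure for the sex-acts analysis. The only calculation is for the primary outcome, used here to set a realistic number analysed. Inputs, from Power and sample size: control rates of 50% at CDOP and 55% at MTAA; an intervention rate of 80% at both; and the stated requirement, "80 % power and α = 0.05, we will require 78 patients in CDOP and 108 patients in MTAA facilities".

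With n per arm = [1.96·√(2p̄q̄) + 0.8416·√(p₁q₁ + p₂q₂)]² / (p₂ − p₁)²:
- CDOP (0.50 vs 0.80, p̄ = 0.65): (1.322 + 0.539)² / 0.09 = 38.5, so 39 per arm, 78 in total; 78 / 0.75 = 104.
- MTAA (0.55 vs 0.80, p̄ = 0.675): (1.298 + 0.537)² / 0.0625 = 53.9, so 54 per arm, 108 in total; 108 / 0.80 = 135.
- Sum: 104 + 135 = 239, as stated. Evaluable: 78 + 108 = 186.

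**2. What each model estimates.** Let π be the proportion of structural zeros and μ the mean among the rest. Mean acts = (1 − π)μ, so

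ratio of means = [(1 − π₁)/(1 − π₀)] × (μ₁/μ₀).

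Log-link Poisson and negative binomial models target the left-hand side and differ only in variance. A zero-inflated fit reports μ₁/μ₀ and the odds ratio [π₁/(1 − π₁)] / [π₀/(1 − π₀)].

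| Structural zeros, control → intervention (μ unchanged) | Ratio of means | Count-part ratio | Odds ratio for structural zeros |
|---|---|---|---|
| 50% → 65% | 0.35/0.50 = 0.70 | 1.00 | (0.65/0.35)/(0.50/0.50) = 1.86 |
| 40% → 55% | 0.45/0.60 = 0.75 | 1.00 | (0.55/0.45)/(0.40/0.60) = 1.83 |

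This step needs no simulation.

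**3. False-positive rate.** The article gives no count distribution, so three were assumed: 186 analysed, 93 per arm, no true effect, no covariates, 700 simulated trials each (Monte Carlo standard error about 0.8 points near 5%). The choice between negative binomial (NB) and zero-inflated negative binomial (ZINB) was made by AIC without using arm. Rejection at nominal 5%:

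| Reading | NB mean 10, dispersion 2, no extra zeros | NB mean 10, dispersion 1, 20% structural zeros | NB mean 16, dispersion 1, 40% structural zeros |
|---|---|---|---|
| ZINB selected | 9.3% | 96.3% | 98.9% |
| Selected model, count coefficient only | 5.6% | 6.4% | 4.9% |
| Selected model, joint 2-df test if ZINB | 5.4% | 6.0% | 5.6% |
| Selected model, either ZINB part counts | 5.6% | 8.6% | 9.3% |
| Free choice of NB or either ZINB part | 7.3% | 9.7% | 9.4% |
| NB fixed in advance | 5.1% | 4.7% | 1.7% |
| Robust-error Poisson fixed in advance | 5.4% | 7.4% | 6.3% |

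For comparison, two independent 5% tests give 1 − 0.95² = 9.75%. In the first column, ZINB standard errors failed in 26% of trials; these were kept on NB.

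**4. Where a true effect shows up.** Assumed: 186 analysed, mean 12 among non-structural participants, dispersion 0.8, structural zeros 50% → 65%. Two independent sets of 300 simulated trials gave:

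| Test | Rejection rate |
|---|---|
| Zero-part coefficient | 51% and 56% |
| Joint 2-df test | 41% and 43% |
| Robust-error Poisson (ratio of means) | 23% and 26% |
| Count-part coefficient | 8% and 3.7% |

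Under no effect with the same distribution, the joint test rejected in about 5% and reading either coefficient in 9.7%.

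**The case against.** The strongest reply has three parts.

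*It is an ordinary model family, condensed in an article, and an analysis plan may settle the rest.* Much of this stands. A test for over-dispersion and a threshold for moving to zero inflation belong in an analysis plan, and their absence is no finding. What remains is that the stated rule itself permits a branch with a different effect measure.

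*Selecting a model does not by itself inflate error.* This stands. With one named test, rejection stayed between 4.9% and 6.4%. The article never says that either coefficient may count as success; it leaves that open.

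*The zero-inflated model can be the more powerful analysis.* This also stands. In step 4 the zero part and the joint test both beat the ratio of means.

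Three stronger readings are therefore tempting but not supported:
- A reader might infer gross error inflation from Poisson being listed first. Model-based Poisson did reject in 61% to 66% of the null trials in step 3, but the over-dispersion clause moves such data to negative binomial, so this is not the plan's error rate.
- A reader might infer that a real reduction would be lost. It leaves the count part but appears in the zero part of the same fit.
- A reader might infer that every switch changes the effect measure. Poisson to negative binomial does not.

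Nor do the documents show how often the zero-inflated branch would be used; the selection rates above reflect assumed distributions.

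**Conclusion.** The point holds in a limited form. For one secondary outcome, the stated rule allows a data-driven move from a ratio of mean acts to a pair of coefficients that measure something else, without naming which is the treatment effect. The difference can be material: 0.70 against 1.00 in the worked case, which is exact given its inputs. The error-rate cost is conditional: about 9% to 10% at worst if either coefficient or either model may be chosen, near 5% with one named test. Those rates rest on assumed count distributions, no covariates and 186 analysed. The primary test and the 239 are not affected. Severity is low, and the remedy is cheap enough to be worth making.

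**What to change.** State in the plan that the effect measure is the ratio of mean unprotected acts over 3 months, intervention to control. Estimate it with one pre-specified log-link model, such as Poisson quasi-likelihood, with robust standard errors. Use a small-sample correction, since uncorrected robust Poisson rejected in 5.4% to 7.4% of null trials.

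Adjust for the baseline count, which the Data sources section already provides for, and for all three randomisation factors, adding location of primary care provider to the two now listed.

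Report zero-inflated fits as labelled sensitivity analyses, using either the joint 2-df test or the ratio of means implied by both parts, (1 − π₁)μ₁ / [(1 − π₀)μ₀], rather than a single part.

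The cost is a sentence or two and no new data; the Trial status section describes the trial as still being planned. There are two downsides. The ratio of means has less power than the zero part or the joint test when the effect works mainly through more zeros (23% to 26% against 41% to 56% in step 4). It is also sensitive to a few very large counts.

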### Randomization

Participants will be assigned randomly to the intervention or to the control group at the time of the baseline visit. Randomization will be stratified by recruitment site (MTAA versus CDOP programs), location of primary care provider (study site versus other), and type of drug use (injection as a method of drug use versus non-injection drug use). The randomization will be done in blocks of randomized size (varying from four to 10) with computer-generated random numbers. This procedure ensures that the distribution of treatment site and type of drug use will be balanced across intervention and control groups. It also prevents study staff from learning the randomization pattern, which becomes obvious in a fixed block-size scheme. The study statistician will generate the randomization lists, which will be concealed in sequentially numbered, opaque, sealed envelopes with a signature across the sealing point. Trained research assistants, who are blind to the randomization schedule, will provide the random assignment to participants at the time of randomization.

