### Data sources

In order to measure all outcomes, indicators, and covariates, each study assessment will collect detailed data from study participants. We will use audio computer-assisted self-interview (ACASI) to limit social desirability biases in reporting sensitive behaviors (for example, sexual behaviors) [68]. Interviewers will be trained in the use of the ACASI program and survey to assist respondents as needed. To protect against the risk of loss of confidentiality during and after the trial, all data will be maintained on a password-protected local server. Study datasets will be de-identified prior to analysis.

We will collect the following information:

Demographic characteristics of participants (at baseline), which will include age, sex, race and ethnicity, years of formal education, income, employment status, health insurance, living arrangement including homelessness, number of children (under 18), and history with the criminal justice system (that is, arrests and incarcerations). This information will be used to describe the study sample, to assess for any differences between intervention groups, and to test for selective attrition.

Sexual behaviors: We will collect data on the total number of sex partners in the past 3 months, total number of vaginal sex partners and anal sex partners, total number of unprotected vaginal and total number of anal sex partners, and total acts of unprotected vaginal/anal sex.

Drug use: We will ask about the frequency, duration, and amount of substance use, including alcohol, cannabis, methamphetamine, cocaine, heroin, club-drugs, and mis-used prescription drugs. We will assess injection drug use, including the types of drugs injected and the sharing of needles and other drug paraphernalia (for example, spoons and cotton balls). We will also ask about overdoses and treatment for overdose (that is, the use of naloxone). At baseline, we will measure these behaviors over the 3 months before the interview. These measures will be repeated at 1- and 3-month follow-ups, with adjustments to the recall period.

Utilization of drug treatment services: We will ask the following three questions at baseline and at both follow-up visits: (1) Are you in treatment right now? (2) What treatment are you undergoing? (for example, detox) and (3) How many days have you been in this treatment?

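### The count model for unprotected sex acts omits one of the three randomisation strata and the participant's own baseline count, which costs precision but causes no bias

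*Protocol article*

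**What the plan says.** The Randomization section of the protocol article sets three stratification factors: "Randomization will be stratified by recruitment site (MTAA versus CDOP programs), location of primary care provider (study site versus other), and type of drug use", the last being whether drugs are injected. In Empirical analysis, the primary model is one "which includes covariates for type of drug use (injection/non-injection) and location of primary care provider (study site versus elsewhere"), with recruitment site added in the next sentence, so all three strata are in it.

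The secondary count outcome is defined as "counts of unprotected vaginal and anal sex acts in the past 3 months with any sex partner". According to Empirical analysis it "will be modeled using Poisson or negative binomial regression (if the variable is over-dispersed) or the zero-inflated version of these if necessary". The next sentence gives the covariates: "Type of drug use (injection/non-injection) and the recruitment site (MTAA or CDOP) will be included as covariates". The one after gives the only stated way for anything else to enter: "If other covariates predict missing data, they will also be included as control variables".

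No model in the section names the baseline value of the outcome. Study assessments places the baseline visit before randomisation. Data sources says that every assessment collects detailed data and lists the total of unprotected vaginal or anal acts among the items.

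**The concern.** An analysis should normally reflect the factors that restricted the randomisation. The primary model does so, and the count model, without explanation, does not. A count of sexual acts is also likely to be strongly related to the same person's earlier count, and that earlier count is already being collected. Leaving it out discards prognostic information and leaves any chance imbalance in a skewed variable uncorrected.

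The missing-data clause does not repair this. It selects covariates by whether they predict attrition, which is known only once the data are in. A strong predictor of the outcome that is unrelated to dropout would stay out, and so would a stratification factor.

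At stake is the width of the confidence interval for a secondary outcome, in a trial whose sample size was set for the primary outcome alone.

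**Working it through.** **1. What is named where.**

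| Variable | Stratum | Primary model | Count model |
|---|---|---|---|
| Recruitment site | yes | yes | yes |
| Type of drug use | yes | yes | yes |
| Primary care location | yes | yes | no |
| Baseline count of unprotected acts | – | – | no |

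Primary care location must be known at randomisation because it is a stratum. The Randomization section, when it says what the procedure balances, also mentions only site and drug use. The two-factor wording therefore appears twice beside a three-factor design.

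**2. Evaluable number.** The plan gives no power or precision for the count, so the primary sizing is the only anchor. A two-sample chi-squared test (two-sided 0.05, 80% power, no continuity correction) gives 39 per arm for 50% versus 80% (78 in CDOP) and 54 per arm for 55% versus 80% (108 in MTAA). Dividing by the assumed follow-up rates: 78/0.75 = 104 and 108/0.80 = 135, total 239. This reproduces the plan exactly. The evaluable number is 78 + 108 = 186. Those follow-up rates were assumed in sizing the 1-month primary outcome; using 186 for the count is an assumption.

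**3. Linear approximation.** The documents give no correlation ρ between baseline and follow-up counts, so a range is assumed. Variance ratio = 1 − ρ²; equivalent number = 186/(1 − ρ²); power for a contrast with 80% unadjusted = Φ[(1.960 + 0.842)/√(1 − ρ²) − 1.960].

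| ρ | Variance ratio | Change in SE | Equivalent n | Power |
|---|---|---|---|---|
| 0.3 | 0.91 | −4.6% | 204 | 83.6% |
| 0.5 | 0.75 | −13.4% | 248 | 89.9% |
| 0.7 | 0.51 | −28.6% | 365 | 97.5% |

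**4. Negative binomial simulation.** The formula in step 3 belongs to a linear model, not the planned one. The check used 186 participants, gamma mixing with dispersion 1.5, a mean of about 8 acts, a rate ratio of 0.6, a coefficient of 0.2 on the log rate for primary care location, and 500 runs per scenario. All of these are assumptions. Here ρ is the correlation of the normal scores that generate each person's two underlying rates.

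| ρ | Power, plan's covariates | + primary care location | + location and log(baseline + 1) |
|---|---|---|---|
| 0.3 | 76.0% | 76.2% | 78.0% |
| 0.5 | 77.4% | 78.6% | 82.8% |
| 0.7 | 78.0% | 78.2% | 91.8% |

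The Monte Carlo error of one power figure is about √(0.8 × 0.2/500) = 1.8 points, so the gain at ρ = 0.3 is small and not sharply determined.

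**5. Primary care location alone.** The spread of the estimates over runs went from 0.190 to 0.189 at ρ = 0.5. With a coefficient of 0.5 and no treatment effect it went from 0.197 to 0.192, and 1 − 0.192/0.197 = 2.5%. Across scenarios the change is about 0% to 3%.

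**6. A caution on step 4.** In the four scenarios at ρ = 0.5, the spread of the estimates with both variables added fell from 0.190 to 0.187, 0.194 to 0.181, 0.197 to 0.182 and 0.193 to 0.184, which is about 2% to 8%. In the first of these the average model-based SE fell further, from 0.187 to 0.172 (8%). Rejection under no effect was 6.2% with the plan's covariates and 6.8% with both added. Part of the apparent power gain may therefore come from a model-based SE that is slightly too small.

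**The case against.** The strongest reply is that a journal article condenses the protocol, that baseline adjustment of a secondary outcome is usually left to the analysis plan, and that naming two covariates does not say there are only two. Had the article been silent on covariates, this would be decisive. It is not silent: for the count model it gives a list and then a rule for additions, and neither brings in the third stratum or the baseline count.

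Other parts of the reply stand:

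- Primary care location is worth almost nothing in precision, and nothing in the article suggests that it predicts sexual behaviour. Its case is consistency with the design.
- A reader might infer that the drug-use outcomes are fixed to the primary model's covariates and so also lack their baseline value. The article says only that similar techniques will be used for them, so no covariate list is fixed and no omission is stated.
- A reader might extend baseline adjustment to every secondary outcome. Linkage to care is defined among those who test positive, and entrants report negative or unknown status. Records-based receipt follows an eligibility rule that excludes people who received results of a test begun in the previous 12 months. Neither has a usable baseline value.
- A reader might cite "At baseline, we will measure these behaviors over the 3 months before the interview" as proof that the sexual count is collected at baseline. That sentence is in the drug-use paragraph. Baseline collection of the count rests instead on the general statement about each assessment and on the pre-randomisation visit.

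**Conclusion.** The point holds for the count model. It names two of three strata, leaves out a baseline count that is collected, and admits further covariates only through a missing-data criterion. This is an inefficiency on a secondary outcome. It does not bias the comparison and does not touch the primary analysis.

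The gain from the baseline count runs from small at ρ = 0.3 (about 2 points of power) to substantial at ρ = 0.7 (about 14 points). It depends on correlations, dispersion and a rate ratio that the documents do not give. It would be tempting to quote the linear figures, such as 186 evaluable participants being worth 248 at ρ = 0.5. The planned model is not linear and the simulated gains are smaller, so those figures should not be carried over. Nor do they transfer to binary outcomes: with a logit link, adding a prognostic covariate changes the odds ratio to a conditional one and does not shrink its SE by that formula.

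The change is worth making because it is nearly free, not because the analysis is invalid without it.

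**What to change.** - **Count model:** prespecify recruitment site, type of drug use, primary care location and log(baseline unprotected acts + 1) as covariates, regardless of whether they predict missing data.
- **Drug-use and injection-practice outcomes:** state that the baseline value of the same behaviour is included.
- **Linkage to care and records-based receipt of results:** do not add a baseline value.
- **Recall:** the count is defined over 3 months. Add the log of recall length as an offset only if the recall window for the count differs between visits.
- **Randomization section:** mention all three strata where it describes what the procedure balances.

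The cost is a few sentences, with no new data. Trial status puts the study at the planning stage with recruitment still to start, so the change can be made before any outcome is seen.
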